### Random Allocation

2.6

In this study, the random blocking method will be utilized for the random allocation of samples in the intervention and control groups, based on marital status (single and married) and BMI (< 20, 20–25, and > 25). For this purpose, double blocks will be considered. The two possible blocks are TC and CT, where T stands for the intervention group, and C stands for the control group. Numbers will be generated randomly (with the RANDBETWEEN command in Excel software and ranges 1 and 2), and according to the production values of one of the blocks (for production number 1 CT block, for production number 2 TC blocks) will be selected and samples will be allocated. For instance, two married women with a body mass index of 20–25 have been referred, one assigned to the intervention group and the other to the control group. In Excel software, between numbers one and two, assuming the number two is selected randomly. Therefore, these two people are assigned to the TC block. Accordingly, these two people are assigned to refer to this block in order. The first person enters the intervention group, and the second person enters the control group. Now, if the number one is chosen, these two people will be assigned to the CT block [43].

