### Statistical Analysis

2.13

The data from quantitative variables will be described by calculating the mean ± standard deviation, and qualitative variables will be described in terms of frequency and percentage. To compare variables between intervention and control groups according to the qualitative and quantitative variable nature, the *χ*
^2^ test (if the default is not established, Fisher's exact test) and *t*‐test of two independent samples, analysis of variance, or its non‐parametric equivalent (Mann–Whitney and Kruskal–Wallis) will be used, respectively. It should be noted that checking the defaults in terms of normality (Kolmogorov–Smirnov and Shapiro–Wilk test) and equality of variances (Levene and F test) will be on the agenda. Finally, to compare the mean resilience score between the two intervention and control groups during the study period (before the intervention, right after the intervention, and 4 weeks post‐intervention), and also to control for the effect of intervening factors, repeated measures ANOVA or mixed models will be used for variance analysis. For every outcome, the projected effect size along with its 95% confidence interval will be displayed. The significance level of the tests will be 0.05. The analysis will be conducted using SPSS V.26. The reporting of statistical results will adhere to the Statistical Analyses and Methods in the Published Literature (SAMPL) guideline [53].

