### Potential Cofounders

2.15

At the start of the research, various demographic and medical variables that could create bias will be documented. Additionally, both groups' participants will be required to continue their regular diet and exercise routine throughout the study. To guarantee that participants adhere to the protocol, their food consumption and exercise levels will be evaluated in each session and documented. Eventually, all possible confounders will be statistically examined, and if a significant difference is found between the groups, their impacts on study results will be modified.

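### Section 2.15 adjusts for covariates according to whether they differ significantly between arms, which in effect never admits the stratification factors; the cost is lost precision and a model not fixed in advance, not false positives

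*Protocol article*

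**What the plan says.** Three sections of the protocol article bear on this point.

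- **2.15 Potential Cofounders** gives the entry rule: "all possible confounders will be statistically examined, and if a significant difference is found between the groups", their effect on the results is to be modified, which I read as adjusted for. The candidates are not listed; the section says only that "various demographic and medical variables that could create bias will be documented".
- **2.6 Random Allocation** allocates "based on marital status (single and married) and BMI" in three classes (below 20, 20 to 25, above 25), which gives six strata. Blocks have size two: "The two possible blocks are TC and CT".
- **2.13 Statistical Analysis** lists t-tests and similar tests for comparing variables between groups. For the resilience score over the three occasions it says "also to control for the effect of intervening factors, repeated measures ANOVA or mixed models will be used for variance analysis". It names no factor.

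Nowhere does the article say that marital status, BMI class or any other named covariate is always in the model.

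**The concern.** In a randomised trial a significant baseline difference is a chance event unless allocation failed. It does not show that the variable predicts resilience, and prognostic value is the reason to adjust.

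Used as an entry rule, the test works against the design. Variables balanced by stratification will not differ significantly, so they stay out although the allocation was restricted on them. An analysis that ignores that restriction uses standard errors that are too large for between-woman comparisons. Other variables enter or stay out by chance, so the primary model is unknown until the arms have been compared. At stake are precision in a trial of 56 women and the ability to show that the model was fixed beforehand.

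**Working it through.** **Sample size.** Section 2.5.1 reproduces. The common SD is √((20.61² + 23.38²)/2) = 22.04 and the difference is 69.80 − 48.17 = 21.63. With 5% two-sided error (assumed two-sided) and 90% power, n = 2 × (1.960 + 1.282)² × 22.04²/21.63² = 21.8, so 22 per group. Then 44/0.8 = 55, rounded to 56. Nothing below changes this number.

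**Can a stratification factor ever be significant?** With blocks of two the arms differ by at most 1 woman per stratum. A marital level spans three strata (difference at most 3) and a BMI class spans two (at most 2). With equal arms, the Pearson chi-square is the sum over levels of d²/n, where d is the difference between arms in a level and n its size.

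- Marital status, worst case (3 v 0 and 25 v 28): 9/3 + 9/53 = 3.17, below the critical 3.84. p = 0.075, and Fisher's exact test gives 0.24.
- Marital status with at least 10 women in each level, worst case (7 v 4 and 21 v 24): 9/11 + 9/45 = 1.02, p = 0.31.
- BMI class: a class contributes at most 4/2 = 2, so the sum cannot exceed 2 + 2 + 4/52 = 4.08, below the critical 5.99 on 2 degrees of freedom.

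In 20,000 simulated trials (assumed 70% married, BMI classes 10/35/55%) neither factor was ever significant.

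**Chance entry of other variables.** Each independent variable enters with probability 0.05. The chance of at least one is 1 − 0.95^k. The article does not give k, so this is an assumed range.

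| k | 5 | 8 | 10 | 15 |
|---|---|---|---|---|
| at least one enters | 23% | 34% | 40% | 54% |

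**Effect of leaving out the strata on a single-score t-test.** Let the strata explain a share R² of the variance (assumed). Under near-perfect balance the interval is too wide by about 1/√(1 − R²), and the true error rate is about 2Φ(−1.96/√(1 − R²)). Simulated null trials of 56 women (5,000 per setting, same assumed mix) agree, allowing for incomplete blocks.

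| R² | interval ratio | formula | simulated, unadjusted | simulated, adjusted for strata |
|---|---|---|---|---|
| 5% | 1.03 | 4.4% | 4.5% | 5.0% |
| 10% | 1.05 | 3.9% | 4.2% | 5.1% |
| 20% | 1.12 | 2.8% | 2.9% | 5.0% |
| 30% | 1.20 | 1.9% | 2.3% | 4.9% |

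A second mix (60% married, BMI classes 10/30/60%, 6,000 trials) gave 4.2%, 3.1% and 2.4% unadjusted for R² of 10%, 20% and 30%.

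**Effect on the repeated measures terms.** Null trials with the second mix, three occasions, R² of 10% to 30%, stratum effects constant over time and an assumed correlation between occasions of 0.5 or 0.7, without stratum adjustment:

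- Single-score t-test: 4.0% down to 2.2%.
- Between-group main effect: 3.5% down to 1.2%. Averaging occasions reduces noise but not the stratum effect, so the strata explain a larger share.
- Group-by-time: 4.4% to 5.3%. A constant stratum effect cancels in within-woman contrasts.

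A separate run gave 2.0% to 3.9%, 1.1% to 3.7%, and 4.8% to 5.6% for the change from baseline.

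**The entry rule itself.** One covariate correlated 0.3, 0.5 or 0.7 with a single outcome score, 56 women, assumed effect 0.7 SD:

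| correlation | power, always adjusted | power, adjusted only if significant | type I error, adjusted only if significant |
|---|---|---|---|
| 0.3 | 0.76 | 0.73 | 4.8% |
| 0.5 | 0.84 | 0.74 | 4.4% |
| 0.7 | 0.95 | 0.75 | 3.7% |

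The rule gives away nearly all of the available gain.

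**Baseline as occasion or as covariate.** With equal variances and correlation ρ, the change score has variance 2σ²(1 − ρ). Adjustment for baseline leaves σ²(1 − ρ²). The ratio of the second to the first is (1 + ρ)/2: 0.75 at ρ = 0.5 and 0.85 at ρ = 0.7 (assumed values).

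**The case against.** The strongest reply has four parts.

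1. *Baseline is not left out.* A reader might infer from 2.15 that baseline resilience counts only if it differs between arms. Section 2.13 does not support this: the pre-intervention score is one of the three occasions in the repeated measures model. This part stands. What remains is the smaller point that baseline is generally used more efficiently as a covariate.

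2. *The t-test figures are not those of the main resilience analysis.* A reader might take the error rates of 4% down to 2% as applying to every resilience result. They apply to single-score comparisons, and the main effect is similar or worse. The group-by-time or change contrast stays near 5% when stratum effects are constant over time. This also stands, although the article does not say which term is primary, and stratum effects that change over time would not fully cancel.

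3. *The error is on the safe side.* A reader might infer that choosing covariates by significance inflates false positives. No calculation here shows that: every departure shown for the single-score test or the main effect is below 5%, and the change contrast is near 5%. The chance-entry percentages are not error rates.

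4. *The rule says if, not only if.* Section 2.13 promises control for unnamed factors without that condition, and an analysis plan may name them. It is true that exclusivity is inferred. But 2.15 states the one rule that the article gives, and that rule is unsound as written. This is not missing detail.

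One further limit: balance is guaranteed for the BMI classes among the women randomised. BMI tested as a continuous variable could still differ by chance, as could the classes after dropout.

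**Conclusion.** The point holds as one about an unsound stated rule. Testing between arms cannot in practice admit the two factors on which allocation was restricted, and it lets chance decide on the rest.

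The size depends on the analysis. Single-score comparisons and the between-group main effect are conservative, at about 4% falling to between 1% and 2% for an assumed R² of 10% to 30%. At 5% the loss for a single score is negligible (4.5%). The change from baseline is essentially unaffected under constant stratum effects. The R² values, stratum mix, correlations and number of candidate variables are all assumptions, since the article gives none of them.

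The documents do not support a claim of inflated type I error, nor that baseline resilience is ignored. The loss is precision and a model not fixed before the arms are compared. The change should be made because it is nearly free, but the trial's validity does not depend on it.

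**What to change.** Replace the last sentence of section 2.15 along these lines: the primary resilience model always includes marital status and BMI class as used for stratification, merging a BMI class that turns out very small with its neighbour, and uses the baseline score as a covariate for the two post-intervention scores. No covariate is selected by testing for differences between arms. Section 2.13 should refer to this list in place of its unnamed factors.

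The cost is wording and a few degrees of freedom out of 56 women: one for marital status, two for BMI class and one for baseline. Sample size and procedures do not change. The Consent section describes sampling as under way, so the change can be made and dated before the arms are compared, provided that comparison has not yet taken place.

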### Limitations

2.16

Our research might encounter various constraints. Since it is a public study, participants are aware they are engaging in an intervention entitled the Effect of Hypnotherapy on the Resilience of Women with PCOS, and bias is probable in the research outcomes. Subsequently, a random assignment of participants can help attain equilibrium in sociodemographic traits. One of the limitations of this study was the relatively short follow‐up period of 4 weeks. This duration is chosen due to the challenges posed by the COVID‐19 pandemic, during which the study will be conducted. Extending the follow‐up period beyond 4 weeks risks a significant loss to follow‐up due to the uncertainty and constraints experienced by participants during the pandemic. However, we acknowledge that a longer follow‐up period would provide more robust insights into the sustainability of the intervention's effects. Future studies are recommended to include longer follow‐up periods to evaluate the long‐term impact and efficacy of hypnotherapy in improving resilience and other psychological outcomes in women with PCOS. Another drawback of this study is the reliance on self‐reporting tools, and the potential for memory mistakes, ambiguity, sociocultural issues, and personal biases influencing the outcomes is unavoidable. The consultative nature of the intervention and the non‐blinding and concealment of the allocation status of the participants from the researcher's point of view will make performance bias possible in the present study. Last but not least, the possibility of a placebo or confounding effect remains in this protocol since participants in the experimental group receive significantly more interaction with the clinical team compared to those in the control group.

## Ethics Statement

The trial has been approved by the Ethics Committee of Mazandaran University of Medical Sciences (IR.MAZUMS.REC.1400.11670) and prospectively registered with the Clinical Trial Registration Center of Iran on May 4, 2022: (IRCT20161126031117N12).

## Consent

All the moral rights of the participants are preserved in this study. The consent of all the participants and the confidentiality of their information are promised in this intervention.

All participants will be fully informed about their role, and their information will be kept confidential. They will also be asked to complete a written Informed consent form, which emphasizes that their participation is optional and they can withdraw at any time, and include this statement in the ethical approval section of the manuscript. Due to the intervention's nature, this study poses no adverse effects or harm. To the best of our understanding, the research will not lead to any adverse effects. Every 6 months, a report will be sent to the auditor. We will communicate the findings of this study to important stakeholders by presenting at relevant seminars and publishing in peer‐reviewed journals.

Recruitment was originally scheduled to begin in May 2022, but due to a substantial rise in COVID‐19 cases and the center's inability to refer PCOS women, the process was delayed. As a result, in February 2023, the sampling phase commenced, and it is presently ongoing.

## Data Availability

Data sharing not applicable to this article as no data sets were generated or analysed during the current study.
